### Study participants and recruitment

Potential participants will need to provide written informed consent before undergoing any trial-related procedures, including screening. Eligible participants will have a history of T1D with a duration of diabetes less than 24 months from diagnosis and be positive for at least one autoantibody (box 1). Participants will be excluded if they have a history or evidence of severe organ dysfunction, unstable T1D, pregnancy, malignancy, active autoimmune thyroid disease, active clinical infection, hepatitis B or C, HIV and/or organ transplantation (box 2).
Box 1Inclusion criteriaType 1 diabetes18–50 years of ageDuration of diabetes less than 24 months from diagnosisAt least one positive autoantibody (anti-islet cell, anti-GAD, anti-IA2, anti-ZnT8)Written informed consent
Box 2Exclusion criteriaHypersensitivity to aldesleukin or any of the excipientsHistory of severe cardiac diseaseHistory of malignancy within the past 5 years (with the exception of localised carcinoma of the skin that had been resected for cure or cervical carcinoma in situ)History or concurrent use of immunosuppressive agents or steroidsHistory of unstable diabetes with recurrent hypoglycaemiaActive autoimmune hyperthyroidism or hypothyroidismActive clinical infectionMajor pre-existing organ dysfunction or previous organ allograftWomen who are pregnant, lactating or intend to get pregnant during the studyMen who intend to father a pregnancy during the studyDonation of more than 500 mL of blood within 2 months prior to aldesleukin administrationParticipation in a previous therapeutic clinical trial within 2 months prior to aldesleukin administrationAbnormal ECGAbnormal full blood count, chronic renal failure (stages 3–5) and/or evidence impaired liver functionPositive HBsAg or HepC serology or HIV testAny medical history or clinically relevant abnormality that is deemed by the principal investigator and/or medical monitor to make the patient ineligible for inclusion because of a safety concern

Potential participants can be informed of the study by several different systems depending on geographical location and participant preference. For local recruitment potential participants will be identified by their treating physicians, diabetes nurses and research nurses at Addenbrooke's Hospital or approved patient information sites. The contact details of identified potential participants, with their agreement, will be passed to the study team. For national recruitment participants who have registered with the ADDRESS-2 register^24^ or the D-GAP study^25^ will be contacted to determine whether they are interested in enrolling in the study. Details of the study will also be provided to patient groups and charities and will be posted on http://www.clinical-trials-type1-diabetes.com. There will also be a Facebook page and twitter feed for this study.

### The DILT1D study outcome measures

The primary endpoint is based on the percentage of CD4 Treg (defined as CD3CD4CD25^high^CD127^low^) cells within the CD3 CD4 T-cell gate following treatment with IL-2 as measured by fluorescence-activated cell sorting (FACS). The maximum value observed in each patient's profile over the first 7 days of the follow-up period will be identified and the percentage change from the baseline value defines the primary endpoint.

The following secondary outcomes will be measured following IL-2 treatment:
Change in Treg number, phenotype and proliferation will be measured by FACS.Change in Treg cell epigenetic profile.Change in Teff number, proliferation and phenotype will be measured by FACS.Change in lymphocyte cell number, proliferation and phenotype subsets and NK and NKT cells will be measured by FACS and full blood count.Change in cytokines and soluble receptors.Change in metabolic control as measured by self-monitoring of blood glucose, laboratory measurement of blood glucose and glycated haemoglobin (HbA1c) and C-peptide.

The following exploratory endpoints will be measured:
Change in intracellular T and NK cell signalling will be measured ex vivo by FACS following IL-2 treatment. An in vitro dose–response to IL-2 will also be performed to assess durable changes in intracellular T-cell signalling.Change in Treg function will be measured by T-cell suppression assay.Change in T cell, NK and peripheral blood mononuclear cell gene expression.Participants will be characterised for genotypes at T1D susceptibility genes related to the IL-2 pathway.

#### Safety assessments

Safety and tolerability assessments will include clinical history, insulin use, physical examination, temperature, blood pressure, heart rate, 12-lead ECGs, glucose, HbA1c, clinical laboratory tests and adverse event recording.

### FACS measurements and mechanistic analysis

The FACS for Treg (CD3, CD4, CD25, CD127) counts and proportions (%) that define the primary endpoint will be performed at the Department of Immunology, Addenbrooke's Hospital, Cambridge, a clinical laboratory that has been approved for good clinical practice. This assay will be carried out in a blinded fashion without the operators knowing the dose allocation for participants. The non-clinical mechanistic analysis for the secondary and exploratory endpoints for FACS immunophenotyping, Treg epigenetics, intracellular T and NK cell signalling, T-cell function genotype, gene expression analysis will be performed at the JDRF/Wellcome Trust Diabetes and Inflammation Laboratory, Cambridge Institute for Medical Research, University of Cambridge, Cambridge.

### Statistical methods

As an exploratory dose-finding study a formal sample size calculation is not appropriate. Simulation work shows that a sample size of 40 participants will give informative estimates of the target doses, assuming the underlying dose–response relationship can achieve the target responses within a safe range of doses and the between-patient variability does not dominate the dose–response relationship too much to be of practical clinical use.

A dose–response curve describing the relationship between the primary endpoint and the dose will be fitted for a selection of parametric models. Estimates and SEs for all parameters, including the interpatient variability, will be provided for all models, as well as an assessment of the goodness of fit for each model.^26^ An estimate, SE and 95% CIs will be produced for the doses associated with each of the different modelling assumptions that achieve the target response rates.

The target response rates are those that achieve a:
minimal Treg increase,maximal Treg increase.

However, the numerical values that define these increases will only be defined in the light of the data provided by the initial 10 participants. After analysis by the DDC and following review by the TSC these targets will be fixed for the course of the trial.

Summary statistics of all endpoints measured at baseline will be produced. Continuous variables will report sample size, mean, SD, median, minimum and maximum. Categorical or binary variables will report sample size, counts and percentages.

All secondary and exploratory endpoints measured after treatment will be explored using graphical methods, such as scatter plots, to examine their relationship to dose and other explanatory endpoints measured at baseline. A regression framework will be used to quantify such relationships, allowing for adjustments for baseline covariates and time point; transformations of the response variable will be made where appropriate and allowances for correlations within participants and/or within related endpoints will be made.

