## Methods

### Study design

The DILT1D study is a 9-week, single centre non-randomised, single dose, open label, adaptive dose-finding trial. The study includes 12 visits: a screening visit, a treatment day, five visits to monitor the response to a dose of ULD IL-2, four visits to monitor the duration of response and a final follow-up visit on day 60 (figure 1). The DILT1D study has two phases: a learning phase and an adaptive phase. At the start of the study (learning phase) the first 10 participants will receive doses 0.04, 0.16, 0.6, 1, 1.5×10^6^ IU/m^2^ of IL-2, in ascending order with each of the doses being given to two patients before escalating the dose, and with at least a week between pairs of recruits. In the subsequent adaptive phase the data will be analysed sequentially after each participant is observed by fitting a candidate set of statistical models to the dose–response curve. Each model will provide an estimate and SE of the doses that achieve the two targets of a minimum Treg increase and a therapeutic Treg increase. Each model will also provide a recommended dose to assign to the next patient. The choice of doses will be approved by a dose determining committee (DDC) in the light of the reports and recommendations provided. The maximum dose of IL-2 that can be assigned is 1.5×10^6^ IU/m^2^. The study has been approved by Health Research Authority, National Research Ethics Service (13/EE/0020).

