The report generated from the data by the trial statistician for the DDC to review will include: plots of all the patient profiles (Treg response vs time); plots of the sequence of doses; a scatter plot of the primary endpoint (maximal percentage change of Treg, log-transformed) versus dose; the same scatter plot of the primary endpoint versus dose with superimposed fitted models with 95% confidence bands for a list of statistical models; estimated target doses and CIs; residual plots of each model fitted; raw output from statistical packages to double-check on convergence and finally a choice of dose decisions for future patients. The statistical models will initially include: linear, quadratic, cubic, Emax, Emax4 (four parameter) and logistic (four parameter).

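### As described, the primary dose–response models contain dose only; omitting baseline Treg % leaves avoidable error in the estimated target doses

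*Protocol article*

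**What the plan says.** - **Primary model (Protocol article, Statistical methods).** A curve "describing the relationship between the primary endpoint and the dose will be fitted for a selection of parametric models". No covariate is mentioned.
- **Candidate models (Dose determining committee).** Six forms are listed: three polynomials, two Emax models and a logistic. The fitted curves are overlaid on a scatter plot of the "primary endpoint (maximal percentage change of Treg, log-transformed) versus dose". Again only dose appears.
- **Endpoint (The DILT1D study outcome measures).** The highest value over the first 7 days is taken, and "the percentage change from the baseline value defines the primary endpoint".
- **Other endpoints (Statistical methods).** The paragraph on secondary and exploratory endpoints goes further: "A regression framework will be used to quantify such relationships, allowing for adjustments for baseline covariates and time point".
- **Learning phase (Study design).** Ten participants receive five ascending doses without randomisation, "with each of the doses being given to two patients before escalating the dose". The two target responses are set from these ten and then fixed.
- **Sample size (Statistical methods).** Forty participants, supported by simulation whose inputs are not given. The claim is conditional on between-patient variability not swamping the dose–response relationship.

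**The concern.** On the log scale, change from baseline forces the coefficient of log baseline to be exactly 1. Treg % varies within a person, through biology and through the assay, so the best coefficient is below 1. A participant whose baseline happened to be low will tend to show a larger increase at any dose. The change score does not remove this effect; its fixed coefficient creates it.

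A dose-only model treats this predictable part as noise. The stake is precision. The confidence intervals for both target doses are wider than the data require, in a trial whose sample-size argument depends on between-patient variability staying manageable. With two participants per learning dose, chance differences in baseline can also move the early picture of the curve. The plan provides baseline adjustment for the other endpoints but does not describe it for the endpoint that determines the result.

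**Working it through.** **1. The plan's own figure.** N = 40 cannot be reproduced. The article gives no SD, effect size, target response or simulation setting.

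**2. Model (assumed).** Work in logs, reading the endpoint as log(maximum/baseline). Baseline = person's level + error. The maximum is taken over five follow-up values, because Study design lists five visits to monitor response; I assume all five fall within the 7 days, with independent errors. Let k = between-person SD / within-person SD, and s = SD of individual response / within-person SD. The maximum of five standard normals has variance 0.447. In units of within-person variance:

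- Var(baseline) = 1 + k²
- Var(log change at a given dose) = 1 + 0.447 + s²
- Cov(log change, baseline) = −1, because the baseline error enters both

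So r² = 1 / [(1 + k²)(1.447 + s²)]. This is the share of residual variance that adjustment removes. The correlation of two untreated measurements is k²/(1 + k²).

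**3. Gain at N = 40.** One extra covariate multiplies the variance of the dose terms by (1 − r²) × (N − p − 2)/(N − p − 3). With p = 3 dose parameters (cubic or four-parameter model) the second factor is 35/34. The equivalent number of unadjusted participants is 40 × (34/35)/(1 − r²).

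| k | Correlation | r², s = 0 | Equivalent N | r², s = 1 | Equivalent N |
|---|---|---|---|---|---|
| 1 | 0.50 | 34.5% | 59.4 | 20.4% | 48.8 |
| 1.5 | 0.69 | 21.3% | 49.3 | 12.6% | 44.4 |
| 2 | 0.80 | 13.8% | 45.1 | 8.2% | 42.3 |
| 3 | 0.90 | 6.9% | 41.7 | 4.1% | 40.5 |

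In standard errors:

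- Best case: √(0.655 × 35/34) = 0.82
- Worst case in the table: √(0.959 × 35/34) = 0.99
- No correlation: √(35/34) = 1.015, a 1.5% loss

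These figures apply to the dose terms. The overall level of the curve, taken at the sample mean baseline, gains less.

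**4. Chance error or bias?** A simulation used two participants at each learning dose, a linear model with true slope 1 and residual SD 1 (all assumed), and 1,500 runs per setting. ρ is the size of the correlation between endpoint and baseline, from 0 to 0.7.

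- First ten, no trend in baseline: mean error of the unadjusted slope −0.017 to +0.016. The simulation error is about 0.58/√1500 = 0.015, so this is zero for practical purposes.
- First ten, baseline assumed to drift by 1 SD over the whole recruitment: −0.04 to −0.09 for ρ = 0.3 to 0.7, and near zero after adjustment.
- All 40, with a simplified adaptive rule: +0.14 to +0.19 unadjusted. About +0.17 also appears at ρ = 0 with or without adjustment, so most of it comes from adaptive sampling.

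**5. Size of the chance error in one pair.** Assume an SD of log baseline of 0.25 and a baseline/follow-up correlation of 0.7, with equal variances. A pair mean of log baseline has SD 0.25/√2 = 0.18. This moves that dose's mean log change by 0.3 × 0.18 ≈ 0.05, or about 5%. The pair's total SD is 0.25 × √0.6/√2 ≈ 0.14, so baseline accounts for 0.09/0.6 = 15% of its variance.

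**6. Earlier looks.** The same formula at N = 10 gives factors of 7/6 (linear, p = 1) to 5/4 (p = 3).

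- r² = 4.1%: 0.959 × 7/6 = 1.12 to 0.959 × 5/4 = 1.20, so adjustment raises the variance by 12% to 20%.
- r² = 13.8%: 1.01 to 1.08, neutral to slightly worse.
- r² = 34.5%: 0.76 to 0.82, a clear gain.

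Break-even for p = 3 is r² = 1/5 = 20% at N = 10, 1/15 = 6.7% at N = 20, and 1/35 = 2.9% at N = 40.

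**The case against.** **The article is condensed and does not exclude covariates.** The model list is open-ended ("The statistical models will initially include: linear, quadratic, cubic, Emax, Emax4 (four parameter) and logistic (four parameter"), and a covariate set is often left to the analysis plan. This stands in part: a reader might infer that the trial has ruled out baseline adjustment, and the article does not say so. But it does more than stay silent. It describes the primary curve as endpoint against dose, and two paragraphs later writes baseline adjustment in for the other endpoints. The point is a better method than the one described, using data already collected.

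**Baseline is already in the endpoint.** True, with its coefficient fixed at 1. Only the residual correlation matters, and that is what step 2 measures.

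**A reader might infer that small non-randomised pairs bias the curve.** The documents do not support this. Learning doses are preassigned in ascending order, and later doses follow accumulated data, an optimality criterion and committee decisions. Nothing ties a dose to the participant's own baseline. Imbalance is therefore chance error that averages to zero and is already inside the confidence intervals. Ascending open-label assignment makes drift with recruitment order possible, but no drift is shown.

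**A reader might infer that every interim fit should be adjusted.** Step 6 shows otherwise. With ten participants the extra parameter costs precision in most of the assumed range. This objection stands and limits the fix.

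**The size is assumed, in an exploratory study.** This also stands. At the low end the gain is negligible.

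**Conclusion.** The point holds as one of avoidable imprecision. As described, the primary models leave out a measured predictor that the form of the endpoint makes informative. At 40 participants adjustment would reduce the variance of the dose terms by between about 1% (1 − 0.959 × 35/34) and 33% (1 − 0.655 × 35/34), the equivalent of roughly 40 to 59 unadjusted participants.

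This rests on assumptions: an untreated within-person correlation of 0.9 to 0.5, independent errors over five follow-up values, one baseline measurement, and a log of the ratio to baseline. If baseline were an average of several measurements, the gain would be smaller. Systematic bias is not shown and would need baseline to drift with recruitment order. Nor does the point show that the targets set after participant 10 would be wrong, or that adjustment at that look would improve them.

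**What to change.** - **Final analysis (N = 40).** Fit each candidate model as log(maximum) = f(dose) + b × log(baseline Treg %) + error. Evaluate both target doses, with standard errors and confidence intervals, at the mean log baseline. Report the unadjusted fit alongside.
- **Dose determining committee reports.** Show the adjusted fit as a supplementary display once about 20 participants have accrued. Do not require it at the 10-participant interim.
- **Cost.** One parameter per model and a sentence or two in the analysis plan; the baseline values are needed for the endpoint anyway. If baseline proves uncorrelated with the endpoint, standard errors at N = 40 are about 1.5% larger.

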## Discussion

Previous clinical trials involving the treatment of patients with newly diagnosed T1D with potential immunotherapeutics have embarked on large clinical proof-of-concept trials without first establishing the correct dose of the experimental agent in order to achieve the desired immunological outcome. Doses have been usually derived from experience of an agent in another disease entity such as in the case of teplizumab (non-Fc-binding anti-CD3) where the dose used in T1D is the same as that used in renal transplantation (OKT3).^27^ Similarly, the doses of rituximab (anti-CD20) and abatacept (CTLA-4Ig) when used to treat T1D have been derived from clinical experience in rheumatoid arthritis.^28–31^ In the case of otelixizumab (non-FcR-binding anti-CD3), experience from murine models was combined with limited human data to arrive at a dose. This has led, despite considerable efforts, to suboptimal outcomes in clinical trials of these agents, and in the case of otelixizumab, a complete failure in one trial due to a lack of therapeutic effect in humans.^32^

It is clear that new strategies need to be developed to rapidly determine the mechanisms of action of immunotherapeutic agents in patients with T1D prior to embarking on large phase II/III clinical trials.

The main goal of this adaptive mechanistic trial is to establish the best doses of IL-2 to administer in participants with T1D in order to:
induce a minimal Treg increase,induce a maximal Treg increase.

Secondary goals are:
to determine the duration of Treg response from a single dose of IL-2,to investigate the utility of biomarkers of IL-2 responsiveness in treated individuals.

Administration of a single ULD of IL-2 to participants with T1D will enable the determination of the response of the Treg population in this disease. By monitoring the Treg population over subsequent days and weeks we can determine the duration of the Treg population's increase in frequency and function and the return to baseline. It is essential that the optimal dose and duration of response of Tregs be established in T1D prior to the initiation of any future trials of IL-2. The dose and the frequency of dosing will determine whether aldesleukin is clinically acceptable for the long-term treatment of T1D. An empirically derived dose based on experience in other diseases may not be beneficial in T1D since the treatment protocols used in GVHD and HCV vasculitis gave a large rise in Treg population (eightfold and fourfold rise in Tregs from baseline, respectively) and alteration of Treg frequency is not a feature of T1D. Our aim in T1D will be to cause a small or physiological sustained increase in Treg frequency and function that may be maintained over the long term to induce tolerance to insulin-producing pancreatic β cells. This trial will provide the opportunity to determine the minimum dose of IL-2 that could be used to initiate treatment of patients with newly diagnosed T1D, and, in the future, to test the possibility that ULD IL-2 can prevent the onset of autoimmunity, which occurs many years before disease diagnosis. In addition, it will provide data regarding the duration of Treg response which can be used to estimate the frequency of IL-2 dosing in future trials.

An adaptive trial design is well suited to determine the dose response of Tregs to IL-2 therapy. Tregs are an appropriate biomarker since they are highly responsive to IL-2 therapy in humans at ULD and defects in their function are key to the development of T1D. By use of an adaptive design, following the learning phase of the trial where the first 10 start-up participants receive prespecified doses, Treg data from each participant treated can be used to inform the IL-2 dose administered to subsequent individuals in the trial thereby more efficiently accessing the dose–outcome relationship. In this manner Treg data from all participants enrolled will be used. Compared with a standard dosing trial an adaptive design has the advantage of not having to make definitive decisions prior to trial regarding dose and allocation to predesignated treatment groups.

By targeting the IL-2 pathway, one of the key aetiological pathways causing susceptibly to T1D, it will be possible to examine if IL-2 therapy rectifies known deficiencies by analysis of associated biomarkers. Individual participants will have their T-cell subsets followed longitudinally and characterised by deep immunophenotyping before and after treatment to determine the effects on CD25 and FOXP3 expression. Monitoring for increased proliferation (Ki-67) and the emergence of recent thymic emigrants (CD31 cells, increased T-cell receptor excision circles) will be performed. The stability of Tregs will be determined by phenotype (FOXP3, CTLA-4) and by epigenetic analysis of the regulatory regions of FOXP3 and genes associated with Treg function. Measurement of intracellular pSTAT5 signalling in lymphocytes will establish if qualitative defects in IL-2 signalling in T1D are corrected by therapy. Analysis of this panel of biomarkers may determine whether individual or combinations of assays may be useful in future trials to stratify participants with T1D on their ability to respond to IL-2 treatment.
